### Process measures

We will also consider mechanisms through which MemFlex may impact depressive symptoms. Potential mechanisms have been drawn from previous evidence of processes mediating the effect of autobiographical memory on depression (reviewed in [33]). These processes include: 1) problem solving, measured using the short version of the Means-Ends Problem Solving task [34]; 2) rumination, which will be assessed using the Rumination Response Scale [35]; 3) cognitive avoidance, indexed by the Cognitive Avoidance Questionnaire [36]; and 4) verbal fluency as a measure of executive control, as indexed by the Verbal Fluency Task [37]. Each of these measures possesses adequate psychometric properties and has been previously used in evaluation of autobiographical memory interventions. Parallel forms of these measures will be administered at pre- and post-treatment, allowing us to determine whether change in these factors mediates the effect of MemFlex on depressive symptoms at follow-up.

### Methodological aspects

#### Power analysis and sample size

Although a standard power calculation based on detecting treatment effects would be the conventional approach to determining sample sizes for clinical trials, the main aim of the current Phase II trial is to provide a point-estimate of efficacy, and evaluate acceptability and feasibility of MemFlex, in preparation for later phase evaluations of the intervention in line with UK Medical Research Council (MRC) guidance. Our previous experience with Phase II exploratory trial platforms indicates that 50 participants (25 in each arm) will provide sufficient numbers to estimate outcome, and evaluate feasibility and acceptability, and to generate preliminary process data for this treatment. This will provide a plausible range of point estimates of effect on our set of outcome measures sufficient to guide us in sample size calculations for later phase trial work.

### Blinding

The study will employ a single-blind design. This will be achieved by condition allocation not being revealed until the pre-treatment assessment has been completed. Post-treatment and follow-up assessments will be completed by a blinded assessor.

### Statistical analysis plan

All analyses will be completed by the trial statistician, in accordance with CONSORT guidelines. The effect of treatment condition (MemFlex, psychoeducation) on our co-primary outcome of the number of participants who meet criteria for a major depressive episode at follow-up will be determined using chi square analysis. The effect of treatment condition on our co-primary outcome of the number of depressive symptoms at follow-up and on our secondary outcomes will be analysed using independent samples *t*-tests. Baseline differences on relevant measures will be included as covariates, if appropriate. We will also examine mediation effects to determine any mechanisms of change. Assessment of mediation will be completed according to recommendations of Hayes [38]. Multiple imputation will be used to account for missing data. Intent-to-treat analysis will also be used for those lost to attrition. No interim analyses are to be completed.

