### Participants and recruitment

We will recruit 25 participants per condition (n = 50) with a primary diagnosis of MDD. Inclusion criteria are age over 18 years and currently experiencing a major depressive episode, as assessed using the Structured Clinical Interview for the Diagnostic and Statistical Manual (DSM)-IV (SCID) [31]. Participants will be excluded if their SCID assessment indicates they are experiencing another mood disorder, psychosis, or current alcohol or substance dependence/abuse. Those with a diagnosed personality  disorder or brain injury (assessed by participant report) will also be excluded.

Participants will be recruited in three ways. First, we will recruit from the community via posters and advertisements. Potential participants who make contact after seeing an advertisement will be sent an information sheet. If consent to contact is given, we will then telephone the individual to complete an initial telephone screening. Second, we will recruit from our department volunteer database, which consists of approximately 300 volunteers who have a history of depression and have expressed a wish to participate in research into the disorder. Those on the database will be emailed the study information sheet, and directed to contact the research team if they would like to participate. Again, those interested in participating will then complete an initial telephone screening. Finally, we will also recruit those from clinical facilities who have given consent to be contacted regarding participation in depression research. Recruitment of these participants will follow the same procedure as our database. Following the initial telephone screening, all eligible participants will be invited to complete a SCID and the pre-treatment assessment.

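### For the diagnostic-status co-primary the plan names only a chi-square test, which does not itself give the point estimate that is the trial's stated aim and fits poorly with the planned covariates and multiple imputation

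*Protocol article*

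**What the plan says.** All quotes are from the protocol article.

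- **Statistical analysis plan.** One co-primary is diagnostic status at the 3-month follow-up. The arms are compared on the number of participants "who meet criteria for a major depressive episode at follow-up will be determined using chi square analysis". No effect measure or interval is attached to that test.
- **Same section.** Two further sentences bear on this outcome: "Baseline differences on relevant measures will be included as covariates, if appropriate" and "Multiple imputation will be used to account for missing data". The section also promises: "All analyses will be completed by the trial statistician, in accordance with CONSORT guidelines".
- **Power analysis and sample size.** A conventional power calculation is set aside because "the main aim of the current Phase II trial is to provide a point-estimate of efficacy, and evaluate acceptability and feasibility of MemFlex". On the chosen size it says: "This will provide a plausible range of point estimates of effect on our set of outcome measures", which are to guide the sizing of later trials.
- **Participants and recruitment.** "We will recruit 25 participants per condition (n = 50) with a primary diagnosis of MDD".

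**The concern.** The trial justifies 25 per arm by estimation rather than testing, then names only a significance test for one of its two co-primaries. A planner of the later trial needs the two event rates, the difference between them and its uncertainty. The test statistic supplies none of these.

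The same test also meets two other commitments in its own section badly. A Pearson chi-square on a 2x2 table has no place for a baseline covariate. Its statistic is not an estimate with a standard error, which is what Rubin's rules combine. With imputed outcomes the analyst would hold one chi-square value per imputed table and would have to choose, after the fact, how to turn them into one result. At stake is whether this co-primary is reported as an adjusted estimate that uses all randomised participants, or as a p-value with an estimate added informally.

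**Working it through.** **1. The plan's own figure.** 25 + 25 = 50, which agrees with the stated total. The article gives no alpha, power, event rate or dropout rate, so the size cannot be derived further. Every event rate below is an assumption.

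**2. What the test returns.** For a 2x2 table with cells a, b, c, d, chi-square = N(ad - bc)² / (product of the four margins). With 10/25 v 15/25 in an episode (MemFlex v psychoeducation):

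- chi-square = 50 × (10×10 - 15×15)² / 25⁴ = 50 × 15,625 / 390,625 = 2.00, p = 0.157 (0.258 with continuity correction).
- Reversing the arms (15/25 v 10/25) gives the same 2.00 and the same p.
- The risk differences are -0.20 and +0.20, so the statistic does not carry even the direction.

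**3. What the same table gives as an estimate.** Risk difference = 0.40 - 0.60 = -0.20. SE = √(0.4×0.6/25 + 0.6×0.4/25) = √0.0192 = 0.139. The Wald 95% CI is -0.20 ± 1.96 × 0.139 = -0.47 to 0.07 (Newcombe -0.43 to 0.07). The odds ratio is 0.44 (0.14 to 1.38).

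**4. Precision.** Half-width = 1.96 × √(2p(1-p)/n):

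| Common rate | 25 per arm | 20 per arm |
|---|---|---|
| 30% or 70% | 0.25 | 0.28 |
| 50% | 0.28 | 0.31 |

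**5. Multiple imputation.** Suppose 8/20 v 12/20 are observed, 5 per arm are missing, and m = 50 imputations are drawn.

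- *Risk difference by Rubin's rules.* Average the estimates; total variance T = W + (1 + 1/m)B, where W is the within-imputation and B the between-imputation variance. Result: -0.21, SE 0.149, 95% CI -0.50 to 0.08, p = 0.16.
- *Chi-square.* The 50 values run from 0.32 to 5.13, on both sides of the 3.84 cut-off. Approximate pooling of the statistics (the D2 rule) gives 1.92, p = 0.17, but no estimate or interval.

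**6. Operating characteristics, illustrative only.** Full enumeration of the 26 × 26 outcomes at exactly 25 per arm, two-sided 5%:

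| Quantity | Uncorrected | Continuity-corrected |
|---|---|---|
| Type I error, common rate 50% | 6.5% | 3.3% |
| Type I error, common rate 60% | 6.0% | 2.9% |
| Power, 60% v 40% | 34% | 24% |

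At 25 per arm the uncorrected error is 5.4% at 30% or 70% and 5.5% at 20% or 80%. With 20 to 23 per arm it lies between 4.3% and 5.6% for common rates from 20% to 80%.

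**7. The alternative.** This is a linear model on arm and a baseline covariate with HC3 variance, simulated 8,000 times (control rate 60%, baseline correlation 0.5, both assumed). It held a type I error of 4.9%. Power was 32% against 34% for the uncorrected chi-square at a latent standardised difference of 0.5, and 64% against 64% at 0.8. The half-width was about 0.26.

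**The case against.** **The estimate is available anyway.** Two proportions, a risk difference and an interval come from the table on which the test is run, and CONSORT reporting is promised. This stands. A reader might infer that the main aim fails for this outcome; the documents do not support that. The aim also covers acceptability and feasibility, which the test does not touch. What remains is that the named analysis does not supply the estimate, and that the version readily taken from the raw table is unadjusted.

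**Adjustment and imputation are not impossible.** A reader might infer that a chi-square analysis can never be adjusted or combined over imputations. That is too strong. A stratified (Cochran-Mantel-Haenszel) test exists, although it needs categorised covariates and would have thin strata at n = 50. The conditional covariate sentence can be read as allowing a switch to regression, and it fits the t-test for BDI-II no better. The D2 rule pools chi-square values, and in the example its p-value was close to Rubin's. Still, none of these routes is named, and D2 ends in a p-value.

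**Much of this is SAP detail.** The interval method, continuity correction and pooling rule are commonly left to a separate analysis plan, and their absence from a journal article is no fault. The point rests instead on what the article does fix: a method that does not match its own stated purpose or the two neighbouring sentences.

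**The test is adequate at this size.** Largely true. The excess error is a discreteness effect that peaks near a 50% rate at 25 per arm and largely disappears with slightly fewer observed. The adjusted model offers no clear gain in power.

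**Conclusion.** The point holds in a limited form. For one of two co-primaries, the article names a test that gives no size, direction or interval, while it justifies its sample size by estimation. A plain chi-square also does not directly carry the covariates and multiple imputation planned beside it. The aim is not lost; it is not delivered by the named analysis.

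A reader might go further and infer that the test is invalid at this sample size. The figures do not support that: 6.5% and 6.0% apply only at exactly 25 per arm with common rates of 50% and 60%. The case for change is an adjusted, poolable estimate with an interval, with a half-width of about 0.26 at 25 per arm. It is not power. All event rates, the baseline correlation and the effect sizes are assumptions, since the article states none. No figure in the article is shown to be wrong.

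**What to change.** Make the analysis of diagnostic status at 3 months a risk difference (MemFlex minus psychoeducation) with a 95% CI. Take it from a regression on arm and pre-treatment BDI-II, with that covariate fixed in advance: either a linear model with robust (small-sample) variance, or a logistic model followed by standardisation to the risk-difference scale. Fit it in each imputed data set and pool the estimate and its variance by Rubin's rules. Report the 2x2 counts and the chi-square test as supportive.

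The cost is a revised sentence in the analysis plan and a few lines of code. No new data, visits or participants are needed, since pre-treatment symptom scores are already collected. The only downside is a slightly more complex model than a 2x2 test.

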### Ethics and dissemination

All participants will provide informed consent prior to participating in the study. Ethics approval has been granted by the UK National Research Ethics Committee (East of England, 11/H0305/1). MRC, National Health Service and professional ethical guidelines will be adhered to throughout the study. No restrictions have been placed on the publication of results.

## Discussion

Due to high relapse rates for depression, clinical research has begun to target cognitive vulnerabilities which may predispose the individual to future episodes. The flexibility of attention and memory represent well-established vulnerabilities, and previous interventions in this area have been promising (e.g. [20, 29]). The MemFlex programme aims to expand existing interventions by simultaneously targeting multiple inflexibilities, and by beginning to explore the mechanisms through which the flexibility of memory retrieval impacts depressive symptoms. The proposed RCT also advances the field by offering a self-guided, non-computer-based version of flexibility training. This format may engage individuals who may not commit to face-to-face therapy, and the low intensity programme may help to improve depressive symptoms to a point where more intensive therapy, such as cognitive behavioural therapy (CBT), may be completed. Relative to group or one-to-one work, self-guided work may also be more easily offered as an adjunct to CBT, or in situations when access to trained mental health care workers is limited. Coupled with the reduced cost of administration, this increases accessibility of treatment, and may see that the programme is both more affordable and more accessible than existing training options.

Evaluation of novel and innovative treatments is vital in optimising the accessibility of evidence-based intervention, and meeting the aims of the Improving Access to Psychological Treatment initiative in the United Kingdom. If the clinical promise of MemFlex can be established, this trial will be a platform for a larger scale RCT. A Phase III trial will allow us to definitively determine the size of treatment effects, and more comprehensively examine the mechanisms underlying these effects. Novel and innovative intervention options present an exciting avenue for research with clinical samples, and such work may ultimately lead to improved accessibility of psychological treatment.

## Trial status

Recruitment began in January 2015.

## Abbreviations

AMT: Autobiographical Memory Task
AMT-AI: Autobiographical Memory Task with alternating instructions
BDI-II: Beck Depression Inventory II
CBM: Cognitive bias modification
CBT: Cognitive behavioral therapy
DSM: Diagnostic and Statistical Manual
MDD: Major depressive disorder
MRC: Medical Research Council
RCT: Randomised controlled trial
SCID: Structured Clinical Interview for the Diagnostic and Statistical Manual-IV
